### Interventions

3.5

#### Usual care

3.5.1

Post-randomization, all participants will receive four-period usual care provided by the research physician, who will be independent of the outcome evaluation. The usual care in this trial will involve: (1) taking analgesics; (2) immobilizing the neck at a 10°- 20° anteflexion by wearing semi-hard cervical collars when ambulatory (Figure 3), and by inclining pillows while bedridden; and (3) as much bed rest as possible.

**Figure 3 fig3:**
[figure not shown]
Illustration of wearing semi-hard cervical collars. Wearing a cervical collar immobilizes the participant’s neck in forward flexion.

The analgesic diclofenac sodium (75 mg, extended-release) will be prescribed due to it being more readily available than other NSAIDs at GPHCM. Participants will be instructed to take 75 mg of diclofenac sodium orally once daily, with permission to adjust the dosage as needed based on their pain level, but not exceeding 150 mg per day. In cases where pain is poorly controlled despite the maximum daily dose of diclofenac sodium being administered, participants should be encouraged to take opiates with the guidance of the research physician. Each participant will be equipped with a specially-designed diary and required to note the following daily: (1) any analgesics they take; (2) collar-wearing hours; and (3) whether or not they were using inclining pillows. Any unused analgesics must be returned during the fifth-period visit. The quantity of returned analgesics will then be registered in the trial management documents.

Participants randomized to the control arm will receive usual care alone.

#### AMTs

3.5.2

Participants randomized to the experimental group will receive 14 additional sessions of AMT over the four usual care periods, with one session per day in the first period, three sessions in the second period, and two sessions per period in the remaining two periods. It will be administered by a registered therapist who is blinded to the outcome evaluation. The therapist will be required to complete structured training with a self-developed AMT teaching robot (Patent No. CN202311394450.9, CN202311398626.8) and become familiar with the AMT procedure before participating in the pAMTLER.

AMT methodology

This composite intervention procedure begins with pressing-kneading manipulation, is followed by traction manipulation, and concludes with mechanical traction (Appendix S5).

Pressing-kneading manipulation (Figure 4) refers to pressing and kneading the participant’s nuchal region, which is bounded by the 7th cervical vertebra horizontal level and the bilateral mastoid process vertical lines, with the neck anteriorly flexed. The participants will lie supine on the therapy table, with pillows used to gently elevate their heads and necks until the neck is anteriorly flexed to an angle that relieves pain or numbness in the cervicobrachial region. The therapist will sit on a chair at the cranial end of the therapy table, close to the participant’s head. With the palm of one hand supporting the participant’s occiput, the therapist will sequentially perform pressing-kneading along the transverse, zygapophyseal, and spinous process lines within the defined nuchal region using his other hand. He should use the pulps of the index, middle, and ring fingers to press and knead the nuchal muscles along these three process lines in an upward and inward direction, from lateral to medial. To alleviate any muscle tension around the nuchal region, the knead-pressing should be administered at a rate of 30 times per minute, with 3 repetitions on each side. The pressing-kneading force applied should be within the participants’ tolerance, allowing them to feel comfortable and relaxed. Additionally, any tender points identified during knead-pressing should be massaged at a frequency of 50 times every 30 s.

**Figure 4 fig4:**
[figure not shown]
Illustration of pressing-kneading manipulation. *white dot*, mastoid process; *red dot*, the 7th cervical vertebra; *dashed blue box*, the nuchal region for pressing and kneading; *black dashed line*, transverse process line; *white dashed line*, zygapophyseal process line; red *dashed line*, pinous process line.

Traction manipulation (Figure 5) involves using both hands to apply pulling force to the participant’s cervical spine along its longitudinal axis away from the body, with the neck anteriorly flexed to various angles. The therapist will first support the supine participant’s occiput with the palm of his dominant hand, positioning the thumb-index finger web space at the participant’s occipito-cervical junction. The therapist’s other hand will cradle the participant’s chin with the hypothenar. The held occiput and chin serve as the primary contact points to stabilize the participant’s head and neck at a controlled anterior flexion angle and to transmit the manual pulling force. By clamping the upper arms and adducting them toward the chest, the therapist transmits arm- and trunk-generated force through these contact points to produce traction, pulling the participant’s cervical spine away from the torso along the angle of anterior neck flexion. The traction angles will be determined by pathoanatomy causing nerve root compression, and will be dynamically adjusted to achieve patient-reported comfort or reduction in pain and/or numbness. For further details on the traction angles, see Table 1. The traction force will be incrementally increased until visible passive movement is observed in the patient’s toes. Each approximately 30-s traction will be followed by a 10- to 15-s rest interval, which will be repeated 5 times.

**Figure 5 fig5:**
[figure not shown]
Illustration of traction manipulation. With the occiput and chin as contact points, apply a manual pulling force along the forward-flexion angle of the participant’s cervical spine, directed away from the body, until visible passive movement of the toes is observed.

**Table 1 tab1:** Pulling angles during manual intermittent traction.

Pathoanatomy in neural foramen causing nerve root compression		Traction angles
ventral degenerative changes, e.g., hypertrophy of the uncovertebral joints	No vertebral segment consideration required	15° of anterior flexion
dorsal degenerative changes, e.g., hypertrophy of the zygapophyseal joints, herniation of the intervertebral disk	at levels above C4	15° of anterior flexion
	at C4/5	20° of anterior flexion
	at C5/6	25° of anterior flexion
	at C6/7	30° of anterior flexion

The angles in this table, summarized from long-term clinical practice, can be dynamically adjusted within the given ranges to achieve patient-reported comfort or relief of pain/numbness. When both ventral and dorsal changes coexist follow the angle recommended for dorsal changes.

Following the first two *tuina* techniques, participants will be instructed to sit up gradually by assuming a lateral decubitus position. They will independently walk to and lie supine on another therapy table equipped with a self-developed motorized traction machine (Patent No. CN201720316913.3) to receive mechanical traction (Figure 6). Pillows will be used to elevate the supine participants’ heads and necks. They will then be adjusted until the line connecting the acromion, ear apex, and vertex becomes straight, such that the head–neck traction angle is consistent with that during traction manipulation. Meanwhile, a soft cushion will be placed at the cervicothoracic junction to prevent it from becoming unsupported. When the position and angle for mechanical traction is ready, the participants’ heads will be secured to a traction belt in the motorized traction device, and a traction force determined based on their body weight will be gently applied. The traction force will be approximately 10% of the participants’ body weight, typically ranging from 6 kg to 8 kg. This pulling force will be maintained for about 15 min, but will be adjustable according to the participants’ comfort.

**Figure 6 fig6:**
[figure not shown]
Illustration of mechanical traction. *Black dot*, acromion; *red dot*, ear apex; *white dot*, vertex. Adjust the pillows to straighten the line connecting the acromion, ear apex, and vertex such that the participant’s head–neck is in the supine position and has the same traction angle as during manual intermittent traction.

#### Prohibited therapies

3.5.3

Any therapies that might alleviate cervicobrachial pain beyond usual care will be prohibited during study participation, including dehydrating agents, neurotrophic drugs, skeletal muscle relaxants, Chinese herbal medicine, acupuncture, cupping, physical therapy and exercise therapy. Participants who consider pain reduction to be insufficient may seek alternative therapeutic options, but will be withdrawn from the trial.

### Outcomes

3.6

#### Primary outcome measurements

3.6.1

Measures that indicate the feasibility of the future full-scale RCT will serve as primary outcomes. They will be:

enrolment rate: the proportion of recruited participants who are randomized.weekly enrolment rate: the number of participants to be randomized per week over the trial recruitment duration.drop-out rates: the proportion of participants who either withdraw or are lost to follow-up at the initial visits of the 2nd, 3rd, 4th, or 5th periods.retention rates: the proportion of non-dropout participants (i.e., those completing all follow-up measurements) at the initial visits of the 2nd, 3rd, 4th, and 5th periods.adherence rates: the proportion of participants completing the planned number of treatment sessions after randomization (the proportion completing 14 sessions of AMT in the experimental group and attending 4 usual care prescriptions in the control group, respectively).completion rates of efficacy-related outcome measures: the proportion of completed efficacy outcome measures relative to those intended for assessment at the initial visit per period.completion rates of cost-related outcome measures: the proportion of completed cost outcome measures relative to those intended for assessment at every visit during the trial.

#### Secondary outcome measurements

3.6.2

Measurements intended for efficacy assessment in the future definitive trial will be designated as the secondary outcomes. These secondary outcome measures are scheduled to be assessed prior to treatment administration during each period’s initial visit (as shown in Figure 2), and outlined below:

pain rating with the NRS, including cervicobrachial pain, upper extremity pain, neck pain, and shoulder pain.numbness in the upper extremities graded by the NRS.muscle weakness recorded by grip strength using a hand dynamometer (CAMRY EH101) in kilograms.upper extremity disability assessed by the quick disabilities of the arm, shoulder, and hand questionnaire (QuickDASH)neck disability scoring with the neck disability index (NDI)NSAID and opiate consumption per period documented in patient diaries.work-productivity impairment evaluated with the work productivity and activity impairment questionnaire: cervical radiculopathy (WPAI: CR)quality of life quantified with the 5-level version of the euroqol 5-dimensional descriptive system (EQ-5D-5L)emotional well-being measured by Zung’s self-rating depression scale (SDS) and Zung’s self-rating anxiety scale (SAS)

The NRS is a horizontal bar or line evenly segmented by 11 integers, in which “0” on the far left represents “no pain” while “10” on the far right indicates “the worst pain imaginable” (34). It is a popular scale for quantifying pain intensity without usage barriers across cultures and languages (35), and has also been well-validated among patient populations with musculoskeletal pain (36–40). Participants will be instructed to circle one number on the NRS to represent the amount of pain that they are experiencing at the time of evaluation (40). Clinically meaningful pain relief can be concluded when a reduction of at least 30% or 2 points is observed on the NRS (41). Given its recommendation for assessing non-pain subjective experiences, we employed NRS in our study to quantify numbness in the upper extremities (42).

The NDI is an extensively tested self-rated scale for diminished neck function due to pain-related conditions in everyday activities (43). This patient-based questionnaire consists of 10 items scored from 0 to 5, with higher scores corresponding to greater perceived handicaps (44). The total score can be reported as raw points from 0 to 50, or as a percentage of the maximal raw points (45, 46). A validated Chinese version of the NDI will be used in this trial (46), with raw points serving as the scoring method (45). Items on the NDI that are not applicable to respondents’ lives may be omitted, but no more than two. These missing items will be replaced by the average score of the answered items (45). 7 points has been suggested as the minimum clinically important difference (MCID) for NDI among populations with CR (47, 48).

The QuickDASH is a well-recognized patient-reported outcome measure designed to determine the extent to which upper-extremity incapacities impact daily routines, social events, and recreational activities (49, 50). It contains 11 items (3 for symptoms and 8 for function) scored from 1 to 5 on a 5-point Likert scale, with an optional additional module that will be omitted in this trial due to its rare use in patient settings (51). Among the 11 items, only one item related to function can be missing (52). The score of the answered items in QuickDASH can then be converted into a 0-to-100 scaled score using an e-tool provided on the official website (53). A greater converted value indicates greater perceived upper-extremity impairment. The Chinese simplified version QuickDASH (54, 55) with a recommended 14-point MCID (56) will be used in our trial.

The EQ-5D-5L is a readily available generic health status instrument which has shown reliability and validity on musculoskeletal problems (57). It consists of a visual analog scale (EQ-VAS) from 0 to 100 and a five-item descriptive system, with each item having five response levels of severity (58). The digits which participants mark on the EQ-VAS represent their perceived overall health on the day of being interviewed. The five ticked response levels in the descriptive system can be derived into a 0-to-1 index value employing a country-specific ‘value set’ to express a health state profile. Higher EQ-VAS and EQ-5D-5L index values both reveal a better quality of life. In our trial, a Chinese version of EQ-5D-5L obtained from the official website (59) and the China-specific ‘value set’ (60) will be applied. However, the EQ-5D-5L index values will be converted into quality-adjusted life years (QALYs) to inform economic evaluations of interventions.

The SDS (61) and SAS (62) are self-administered instruments for rating depression and anxiety severity based on the frequency of affective and somatic symptoms during the preceding week. Each contains 20 questions scored from 1 to 4 on a 4-point Likert scale based on the perceived frequency, all yielding a raw summation range of 20 to 80. The raw summations will be converted into index scores by multiplying them by 1.25. The index scores can categorize depression as nil (25–49), mild (50–59), moderate (60–69), or severe (70+), and anxiety as nil (25–44), mild (45–59), moderate (60–74), or severe (75+) (63). The Chinese versions (64, 65) which have been demonstrated to have extensive reliability and validity among the Chinese population (66, 67) will be administered in our trial.

The WPAI: CR is a revised questionnaire constructed by specifying “cervical radiculopathy (CR)” in the Work Productivity and Activity Impairment Questionnaire: Specific Health Problem V2.0 (WPAI: SHP). The WPAI: SHP is a six-item patient-reported instrument created for capturing the amount of work time missed, on-the-job effectiveness reduced, and daily activity impairment during the previous 7 days due to a specific health problem (68, 69). The official user guide encourages adapting the WPAI: SHP to any specific health problem by inserting the name of the disease or condition of interest wherever the word ‘PROBLEM’ appears in the WPAI: SHP template (70). In our trial, CR-related work productivity loss will be quantified based on the revised WPAI: CR through per cent work time missed, impairment while working, overall work impairment and activity impairment (71). Greater values indicate less productivity.

Additional secondary outcome measures will include adverse event rate (AER), adverse reaction rate (ARR) and intervention cost. Any undesirable experiences from which participants suffer post-enrolment will be identified as adverse events (AE), and those associated with the intervention will be defined as adverse reactions, while those that result in hospitalization, loss of ability to work, disability, congenital deformity, or death will be listed as serious adverse events (SAE). Any AE during the study will be recorded. The cost of intervention will be based on a societal perspective, and composed of direct medical costs (DMC), direct non-medical costs (DnMC) and indirect costs (IDC) (72). The composition of direct costs are detailed in Table 2, and the composed item cost will be obtained by resource volumes multiplied by their respective unit costs (73). The IDC will be estimated using the human capital approach, which is the product of labor loss time and the unit labor value (72–74). In this trial, labor loss time will encompass the work time missed by both participants and their accompanying family members. The unit labor value will be based on the per capita GDP of Guangzhou in 2024 (73). DMC, DnMC, and the accompanying family’s missed work time will be collected at every visit. The participants’ missed work time will be collected via the WPAI: CR.

**Table 2 tab2:** Composition and determination of direct costs.

Cost composition	Basis for unit cost calculation
DMC resulting from registration, magnetic resonance imaging, NSAIDs and opiates, cervical collars, and AMTs	price summary list of basic medical services in Guangzhou
DMC resulting from adverse reactions	actual costs incurred during the trial
DnMC resulting from round-trip travel, meal and lodging	actual costs incurred during the trial

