## Introduction

1

Cervical radiculopathy (CR) is a term used to describe a consequence triggered by mechanical compression of nerve roots within the neural foramen due to age-related degenerative changes in the cervical spine, i.e., herniated disk material, hypertrophied facet joints, and/or uncovertebral joints (1–5). It is a prevalent, debilitating cervical spine condition characterized by pain in the cervicobrachial region and abnormal neurologic signs along the path of innervation of the affected nerve root, including paraesthesia, numbness, muscle weakness and diminished deep tendon reflexes. The annual incidence has been reported to be between 0.83 and 1.79 per 1,000 person-years, with an estimated prevalence from 1.21 to 5.8 per 1,000 (6). CR is frequently described as a self-limiting disorder with a favorable prognosis (7, 8). However, pain during the first weeks to months is often excruciating (9), and most patients report experienced continuous, fluctuating pain for up to 24–36 months before achieving complete recovery (10, 11). Such pain contributes to impaired physical function, poor mental well-being, limited regular activities, and isolated social life (12–14). It has been reported that approximately 352.0 cases per 100,000 individuals worldwide have suffered from disability resulting from CR over the past three decades (15). Patients with CR are vulnerable to experiencing varying degrees of work ability impairment due to both physiological disturbances and psychological distress (13, 14, 16). Hence, they may be at a higher risk of exclusion from the labor market due to frequent sick leave, work absenteeism, and even failure to execute work duties (13, 14). Patients with CR are also believed to experience poorer economic outcomes as a result of work productivity loss, with an estimated average willingness-to-pay far exceeding $38.0 per month for a 1-point reduction in pain (17).

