The TSC will consist of a principal investigator ([name]), a clinical research methodologist ([name]), a spinal surgery expert experienced in clinical trials ([name]) and the following independent members: a consultant orthopaedist and chair ([name]), a CR patient, and a public involvement representative. Besides approving the study protocol and the trial’s operational guidelines, the TSC will regularly convene to monitor protocol compliance in the administered trial, review the safety data, and resolve any problems from the TMG. Any SAE will be reported to the TSC post-haste, and submitted to the GPHCM Ethics Committee within 24 h. The TSC has the discretion to discontinue any patient’s participation in the study due to safety precautions.

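### The SAE list has no life-threatening or medically important category and leaves loss of ability to work unqualified, so expedited reporting can miss a dangerous event and classification may be inconsistent

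*Protocol article*

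**What the plan says.** Section 3.6.2 first sets a wide definition of an adverse event: "Any undesirable experiences from which participants suffer post-enrolment will be identified as adverse events (AE"). It does not exclude symptoms of the disease under study and does not require worsening from baseline. Seriousness is then defined by result: "those that result in hospitalization, loss of ability to work, disability, congenital deformity, or death will be listed as serious adverse events (SAE").

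Section 3.8 attaches the expedited duty to that class: "Any SAE will be reported to the TSC post-haste, and submitted to the GPHCM Ethics Committee within 24 h". The same section says that no independent data monitoring committee will be set up. It gives the steering committee regular review of safety data, and it has research assistants follow every AE until it resolves.

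On work, the Introduction says: "Patients with CR are vulnerable to experiencing varying degrees of work ability impairment due to both physiological disturbances and psychological distress". It goes on to describe a possible risk of leaving the labour market "due to frequent sick leave, work absenteeism, and even failure to execute work duties". Section 3.6.2 describes the parent instrument of the WPAI: CR as built for "capturing the amount of work time missed, on-the-job effectiveness reduced, and daily activity impairment during the previous 7 days". It uses the WPAI: CR both as a secondary outcome and as the source of participants' missed work time for indirect costs.

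**The concern.** There are two separate weaknesses in what the article states.

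**A gap.** The list is closed and depends on consequences. An event that was dangerous when it happened, but was managed without admission and left no lasting result, is not on it. The protocol recognises hazards of this kind: section 3.2 excludes people with NSAID-related bleeding or perforation, while section 3.5.1 prescribes an NSAID to everyone, and the experimental arm also receives neck traction. With no data monitoring committee, the SAE definition is what decides which events are looked at at once.

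**An ambiguity.** Loss of ability to work has no duration, severity or permanence attached. Disability is a separate item, so the work item presumably covers something short of it, but the text does not say what. Work absence is part of this disease and is also measured as an outcome, so staff have no rule for telling a few days off work from a serious event.

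At stake are the timeliness of safety oversight in this pilot and the quality of a definition that may be carried into the full-scale trial.

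**Working it through.** The documents state no SAE rate, safety threshold or safety sample size, so there is no figure to reproduce. The check is textual, with one illustration of size.

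**Step 1. Test the list for a gap.** Take a life-threatening event in a retired participant (section 3.2 admits ages up to 75) that is managed without admission and followed by recovery.

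| Item in section 3.6.2 | Met? |
|---|---|
| Hospitalization | No |
| Loss of ability to work | No |
| Disability | No |
| Congenital deformity | No |
| Death | No |

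The event is an AE but not an SAE, so the 24-hour rule in section 3.8 does not apply. It is still recorded, followed to resolution and open to the steering committee's regular review. What is lost is the expedited report.

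**Step 2. Test the work item for ambiguity.** Take a pain flare after enrolment that keeps an employed participant at home for a few days.

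- Is it an AE? On the literal definition, yes.
- Is it an SAE? If the work item covers temporary absence, yes. If it means incapacity of the order of the neighbouring items (disability, death), no. The text does not choose.

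**Step 3. What depends on the classification.** Section 3.7.2 reports AE and adverse reaction rates descriptively by group, and no SAE rate is a named outcome. Every SAE is also an AE, so reclassifying an event as serious or non-serious leaves the AE rate unchanged. The adverse reaction rate depends on association with the intervention, not on seriousness. The efficacy models and the feasibility outcomes do not use the classification. What changes is which events are reported fast and listed as serious.

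**Step 4. Possible size of the ambiguity (assumption).** Let p be the share of participants with an AE that is serious only through work loss. The documents give no value for p. With N = 48 (section 3.1), the expected number is 48 × p and the chance of at least one is 1 − (1 − p)^48.

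| Assumed p | Expected number | Chance of at least one |
|---|---|---|
| 1% | 0.48 | 38% |
| 5% | 2.4 | 92% |
| 10% | 4.8 | 99% |
| 20% | 9.6 | over 99.9% |

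At about 1% the ambiguity is minor. At 5–10% or more it could dominate a short SAE list. The documents do not show which applies.

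**The case against.** The strongest reply is that the list works adequately in practice. Most life-threatening events would enter through hospitalization, disability or death. All AEs are recorded, the management group meets weekly, and the steering committee's review is not limited to SAEs. This stands, and it makes the gap narrow. It does not close it, because none of those routes carries the expedited deadline.

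A second reply is that the work item, read beside disability and death, naturally means real incapacity, and that over-reporting is the safer error in a small single-hospital trial. That reading is reasonable, but the text does not fix it.

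A third is that standard operating procedures, which are not shown, may give guidance on seriousness. They may. The article nevertheless prints an explicit list, and the comment is on that list.

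A reader might go further and infer that SAEs will be routine here, because usual care includes "as much bed rest as possible" and sick leave is common. The documents do not support this. Prescribed rest is not in itself an undesirable experience, unchanged pre-enrolment disease does not clearly qualify, work time missed is not the same as ability to work lost, and no employment or flare rate is given.

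A reader might also infer that an effective treatment would show fewer SAEs for reasons of efficacy and so bias the safety comparison. No SAE rate is an outcome, so no planned comparison would carry that bias.

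**Conclusion.** The point holds in a limited form. The printed SAE list omits life-threatening and other medically important events. An event of that kind without admission, disability, work loss or death falls outside the only expedited pathway, though not outside AE recording or regular safety review. The unqualified work item makes classification open to inconsistency in a population where work absence is a disease feature and missed work is measured separately.

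The size cannot be set from the documents; the range in the table rests wholly on the assumed p. It would be too much to say that the SAE count will fail to reflect serious harm, since hospitalization, disability and death are all listed. This is a narrow safety-reporting defect that is cheap to correct. It rests on reading the list as complete, which is how it is written; no other section extends it.

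**What to change.** In section 3.6.2:

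1. Add two categories to the SAE list: life-threatening event, and important medical event whether or not the participant is admitted.
2. Replace loss of ability to work with persistent or significant incapacity.
3. Do not make seriousness depend on whether the event is attributed to cervical radiculopathy. Causality is a separate judgement, and a deterioration after traction could otherwise be set aside as expected disease.
4. Continue to record short-term work absence as a consequence of an AE where relevant, as well as in the WPAI: CR. That questionnaire covers only loss due to cervical radiculopathy, so it cannot replace the AE record.

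Section 3.8 needs no change, because its reporting rule refers to SAEs and will follow the revised list. The article reports that recruitment began in August 2024, so this would be an amendment with matching CRF and procedure text, and AEs already on file should be checked once against the new list. The continuing cost is a few more expedited reports of medically important events.

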## Objectives

2

The aim of this external pilot study is to ascertain the feasibility of a definitive full-scale RCT that determines whether AMT plus usual care is superior to usual care alone in clinical efficacy and cost-effectiveness regarding cervicobrachialgia reduction. In this study, we will (1) evaluate the recruitment and retention of participants, treatment adherence, and completion of proposed outcome measures to inform the feasibility and acceptability of study design; (2) and estimate the variability of efficacy-related outcomes to preliminarily inform sample size calculation for a future fully powered RCT.

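### Participants' missed work is drawn from the WPAI: CR alone, so work time lost to attending AMT is either missing from its societal cost or mixed into the work-impairment outcome, and the article does not say which

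*Protocol article*

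**What the plan says.** Section 3.6.2 (Secondary outcome measurements) sets out the costing: "The cost of intervention will be based on a societal perspective", made up of direct medical, direct non-medical and indirect costs. Indirect cost follows the human capital approach, as labour loss time multiplied by a unit labour value. Labour loss time covers work missed by participants and by accompanying family, and no cause is specified.

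The two shares have different sources. For the accompanying family, "missed work time will be collected at every visit", together with the direct costs. For participants, "missed work time will be collected via the WPAI: CR". The parent questionnaire is described as capturing missed work time, reduced effectiveness at work and "daily activity impairment during the previous 7 days due to a specific health problem". The same instrument is an efficacy outcome: "CR-related work productivity loss will be quantified based on the revised WPAI: CR", through four scores that include per cent work time missed and overall work impairment.

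Table 2 lists travel, meals and lodging as direct non-medical costs, but not participant time. Section 3.5.2 schedules AMT "with one session per day in the first period, three sessions in the second period, and two sessions per period in the remaining two periods". In section 3.6.1 control-arm adherence is defined by 4 usual-care prescriptions.

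**The concern.** The cost definition is neutral as to cause, whereas the instrument that supplies the participant's share is limited to loss caused by CR. For one trip to an AMT session, a relative's lost hours are recorded directly. The participant's lost hours are recorded only if the participant attributes them to CR.

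Either way of answering affects an outcome. If attendance hours are not reported on the WPAI: CR, they enter no cost component and AMT's indirect cost is too low. If they are reported, the indirect cost is complete, but per cent work time missed and overall work impairment rise in the AMT arm because of treatment attendance, and treatment time cannot be separated from disease time. If participants answer differently from one another, the two effects mix.

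The treatment schedule itself creates the imbalance, so randomisation does not remove it. Work outcomes and costs are among the quantities the pilot pilots for the later trial, whose aim in section 2 is to assess "clinical efficacy and cost-effectiveness regarding cervicobrachialgia reduction".

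**Working it through.** **Attendances (sections 3.1, 3.5.2, 3.6.1).**
- AMT sessions by period: 7 + 3 + 2 + 2 = 14, as stated. Adding the period-5 visit gives 14 + 1 = 15 visits, which matches section 3.1.
- Control attendances: 4 prescriptions, taken as one per period. This is inferred, because Figure 1 is not shown.
- Extra AMT attendances by period: 7 − 1 = 6, 3 − 1 = 2, 2 − 1 = 1, 2 − 1 = 1. The total is 10.

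**Is any period missed by the recall window?** No. The WPAI: CR is given at each period's initial visit and looks back 7 days. The assessments at the start of periods 2 to 5 therefore span the four 7-day treatment periods. The problem is the attribution of hours, not time coverage.

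**Possible size.** The article gives no work hours lost per attendance, employment share or unit labour value, so no cost can be calculated. As an illustration, assume an employed participant, a 40-hour week (160 hours over four periods) and 1 to 4 work hours lost per attendance:

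| Quantity | Formula | Result |
|---|---|---|
| Excess over four periods | 10 × 1 to 10 × 4 | 10 to 40 h |
| Share of 160 h | 10/160 to 40/160 | 6 to 25% |
| Period-1 excess, workdays only | 4 × 1 to 4 × 4 | 4 to 16 h |
| Share of a 40 h week | 4/40 to 16/40 | 10 to 40% |

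The period-1 rows assume 5 of the 7 daily sessions fall on workdays, one of them being the initial visit that both arms attend: 5 − 1 = 4. The four-period rows let every extra attendance cost work time. Using the workday count for period 1 gives 4 + 2 + 1 + 1 = 8 attendances, or 8 to 32 h (5 to 20% of 160 h).

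**Which branch applies?** The questionnaire items and respondent instructions are not reproduced. The description ("during the previous 7 days due to a specific health problem") allows a participant either to include or to exclude hours spent attending treatment for CR.

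**The case against.** The case on the other side has several parts.

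- **Unseen material.** Item wording, respondent instructions and the cost form may be in the case report forms and operating procedures mentioned in section 3.8. This stands as a limit: the WPAI: CR is the only source named, but another could exist. The article nevertheless assigns the two shares to different sources, and that is a stated choice rather than an omitted detail.
- **Cost may be complete.** Someone who leaves work for CR treatment may well report those hours as missed because of CR. That is plausible. The indirect cost is then complete, and what remains is the effect on the work outcome.
- **A net effect is legitimate.** In an add-on comparison, time spent attending is a real consequence of the AMT strategy, so a work outcome that includes it can be defended. This is fair, but the article labels the outcome as CR-related loss, and a net effect can be interpreted only if the attendance part is known. Impairment while working and activity impairment are not directly affected.
- **Limited consequence now.** Section 3.7.2 presents costs descriptively, efficacy estimates are exploratory with 75% intervals, no feasibility threshold depends on this, and the cost-effectiveness aim in section 2 belongs to the future trial. All of this stands.
- **Size.** Participants are aged 45 to 75 and are told to rest in bed as much as possible, so some will lose no additional work. This also stands.

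A reader might infer that one particular outcome is biased in a known direction, for instance that AMT's cost is certainly understated. The document does not support that, because it does not settle which branch holds. A reader might also count all five period-1 workday sessions as the difference between arms. That is a gross count; it ignores the control arm's own initial visit.

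**Conclusion.** The point holds as an unresolved attribution of participants' work time, not as a demonstrated bias in one named outcome. As written, attendance-related work loss is either absent from AMT's societal cost or contained in two of the four WPAI: CR scores, and the data described cannot tell these apart afterwards.

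The exposure differs by about 10 attendances per participant, 6 of them in period 1. Under the assumed 1 to 4 hours, the excess is at most 10 to 40 hours per employed participant, less if weekend sessions cost no work, and zero for those not working. The direction within each branch is clear; the branch and the true size are not. No feasibility conclusion of the pilot is threatened. It is a cheap improvement worth making, because hours that were never recorded cannot be recovered at analysis.

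**What to change.** 1. On the cost form already completed at every visit, next to the question about the relative's missed work, add the participant's own work hours missed to attend that visit, and whether those hours are also reported in the WPAI: CR.
2. Leave the WPAI: CR wording and instructions unchanged. Telling later participants to exclude attendance hours would change what the instrument measures partway through the trial.
3. Count each hour once in the indirect cost: WPAI: CR hours, plus participant attendance hours not already reported there, plus the relative's hours.
4. Report attendance-related time separately by arm.
5. For participants already treated, show visit-based hours only as a sensitivity range and do not add them to the indirect cost. A visit log shows attendance, not work lost, and the hours may already be in the WPAI: CR.

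The cost is one additional form item, a possibly higher stated cost for AMT, and incomplete data. Section 4 reports 33 of 48 recruited by 31 July 2025, so at that date at most 48 − 33 = 15 participants could have the new item from their first visit. The item would still be tested on the form that the later trial is likely to use.
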